## Abstract

**Background:**

Mental health services are most effective and equitable when designed, delivered, and evaluated in collaboration with People With Lived Experience of mental health conditions (PWLE). However, PWLE are rarely involved in health systems strengthening, and when they are, it is limited to specific components (e.g., peer helpers) rather than multi-tiered collaboration in the full continuum of home to community to facility based services. Moreover, programs that do involve PWLE typically involve people with a history of substance use conditions or common mental disorders. The collaboration of People With Lived Experience of Psychosis (PWLP) is especially rare. Therefore, we aim to explore the feasibility of collaborating with PWLP for health systems strengthening in this feasibility trial.

**Methods:**

This pilot cluster randomized controlled feasibility trial will randomize 36 health facilities to a standard implementation arm where primary care workers (PCW) will be trained by mental health specialists (control), or a collaborative care model with added co-facilitation of PCW trainings by PWLP as well as home visits by PWLP to service users (intervention). The intervention condition is referred to as “Strengthening CAre in collaboration with People with lived Experience of psychosis in Uganda” (SCAPE-U). The 36 health facilities will be distributed across six clusters with three clusters in each arm. PhotoVoice will be used to train PWLP to be co-facilitators of PCW training and provide home-based support to service users in the intervention arm. The primary outcomes of the feasibility trial will be the feasibility, acceptability, and safety of collaborating with PWLP. Data will also be collected on individual-level outcomes for PCWs, and service users to inform the feasibility of data collection and obtain effect size estimates.

**Discussion:**

Findings from this feasibility trial will inform a fully powered trial to evaluate the benefits of an implementation strategy characterized by collaboration with PWLP across the continuum of healthcare services.

**Trial registration:**

ClinicalTrials.gov. number: NCT05863572.

Date of registration: May 18, 2023.

URL of trial registry record: https://clinicaltrials.gov/study/NCT05863572?term=NCT05863572&rank=1.

## Background

There is a large global burden of untreated psychosis, with scarcity of evidence-based treatment delivered in low-income countries [1]. The lifetime risk of psychosis is estimated to be 3% globally [2]. Psychosis is associated with significant impairment in all aspects of life, often resulting in social alienation, violation of human rights, and other complications such as higher rates of suicide attempts, substance abuse, and homelessness [3, 4]. Among primary psychoses, schizophrenia is the most prevalent, affecting at least 24 million people worldwide, and has the strongest association with disability [3, 5]. According to the 2019 Global Burden of Disease, schizophrenia carried the heaviest disability weight of all mental disorders. Moreover, compared to the general public, the odds of early death are nearly 3 times higher among persons living with schizophrenia [6].

Although psychosis can be highly disabling, it can be treated, and early intervention can be critical in slowing the progression of psychotic disorders to chronic or more severe stages of disease [4, 7]. Following treatment, one in three people with schizophrenia can experience total remission of symptoms [8]. Early diagnosis and intervention also limit the duration of psychotic episodes and reduce recurrence [3, 7]. Unfortunately, at least two out of three people with psychosis globally do not have access to specialist mental health care [1]. In low- and middle-income countries (LMIC) such as Uganda, more than 80% of individuals with all types of mental health conditions including psychosis have no access or limited access to any form of mental health services owing to lack of a trained mental health workforce, poor infrastructure, and pervasive stigma [9].

Uganda exemplifies low-income countries where the majority of treatment for people living with psychosis (PLWP) is restricted to a small number of psychiatric hospitals. There are almost no mental health services available at primary care and community levels in Uganda for People with Lived Experiences of Psychosis (PLWP) [10, 11]. Moreover, Uganda’s health system is inadequate to provide holistic management for PLWP [4, 9]. Pharmacological treatment is typically the sole treatment with neglect of other essential aspects of evidence-based care including psychosocial interventions, skills training, family psychoeducation, rehabilitation, and reintegration into the community following discharge from hospital [12–14]. A 2018 study conducted at Uganda’s National Referral Mental Hospital found that of 156 service users managed for first episode psychosis, 84% received antipsychotics, whereas only 2% and 13%, respectively, received a vocational plan and multifamily group psychoeducation [15].

The World Health Organization (WHO) recommends a shift from institutionalization of people suffering from mental health conditions to community-based models of care, including integration of mental health services into primary health care systems [16, 17]. The current need in LMIC is to increase availability of evidence-based treatment for PLWP including psychosocial interventions. However, the evidence base for community-based psychosocial interventions for people with psychosis in low-income countries is very limited [18].

In parallel, there have been increased calls to collaborate with People With Lived Experience of mental health conditions (PWLE) to strengthen health systems [19–21]. Collaboration with PWLE during the training of primary care workers has the potential to reduce healthcare workers’ stigma and improve their diagnostic accuracy for mental health conditions [22]. However, most research to date has focused on peer-support programs [19, 23–26], and the vast majority of studies are based in high-income countries. A Cochrane review on the use of peer support for persons with psychosis and other serious mental illnesses found that, in comparison with standard care, peer support may improve behavioral domains such as hope, agency, recovery, empowerment, and personal confidence in addition to mental state [24]. Peer support is reported to have benefits such as reduced hospitalization and better recovery outcomes for persons with serious mental illness [25, 27].

In Uganda, only two studies have looked at PWLE involvement, both using peer support. The BRAIN GAIN feasibility study showed feasibility and acceptability of the peer support intervention for people living with serious mental health conditions [28] while the UPSDIES trial, which looks at empowering mental health services through peer support, is underway [29].

Evidence for other aspects relating to the feasibility of involving people with lived experience in health systems strengthening is scarce. The Brain Gain study at Butabika hospital aimed to promote recovery among inpatient and outpatient service users [28]. Few studies globally, and no studies in Uganda, have evaluated the feasibility and acceptability of collaboration with PLWP across the continuum of services from the facility to the community to the home, with an aim of eventually assessing the impact of such initiatives.

We plan to address these gaps through a strategy called “Strengthening CAre in collaboration with People with lived Experience of psychosis in Uganda” (SCAPE-U) where PWLP are engaged in co-facilitating mental health trainings of primary care workers and community health workers and providing support to families of people with psychosis currently in treatment. By using this comprehensive and continuum of care approach, our hypothesis is that engaging PWLP can improve quality of mental health care (including accuracy of diagnosis and fidelity to treatment in primary health care level), increased help seeking and referral at the community level and improved support for treatment adherence and livelihoods at the family level (Fig. 1). We further hypothesize that this model can facilitate early detection, reduce duration of untreated psychosis, overburdening of hospital services, and ultimately improve the quality of life of PWLP.

**Fig. 1 Fig1:**
[figure not shown]
Conceptual framework of SCAPE-U

## Objectives

This current protocol describes a feasibility study using a cluster randomized controlled trial (c-RCT) design. The pilot study compares implementation as usual for mental health services to the SCAPE-U implementation strategy, in which PWLP collaborates in training primary care workers and community health workers, as well as conducting home visits to service users and their families. The pilot and feasibility study have the following objectives (see Table 1):To assess the feasibility and acceptability of involving people with lived experience of psychosis in mental health trainings and home visits.To determine recruitment and retention rates of SCAPE-U facilitators, service users and their caregivers, primary care workers, and community health workers.To establish the acceptability and feasibility of data collection procedures.To demonstrate the feasibility of trial procedures.To demonstrate the ethics and safety of the study procedures.To describe changes in outcome measures at individual, family, and health system levels.To determine the cost of the SCAPE-U implementation strategy.

**Table 1 Tab1:** Feasibility trial objectives

**Objective**	**Resear**ch questions	**Hypothesis**	**Methods**	**Participants**
**1. Feasibility and acceptability of SCAPE-U**	Is it feasible to train and involve people with lived experience of psychosis in the intervention? Do primary care workers, community health workers and caregivers of service users find it acceptable to have people with lived experience of psychosis as co-facilitators in their trainings/supervision and home visits?	People with lived experience of psychosis can be trained to deliver training and home visits effectively and safely All the key stakeholders of the intervention will find the involvement of people with lived experience acceptable	Qualitative interviews Process notes Adverse event logs (target: fewer than 20% among recruited PWLE)	SCAPE-U facilitators, primary care workers, community health workers, service users and their families, research staff and trainers
**2. Recruitment and retention**	Can we recruit, train, and retain enough PLWP to be SCAPE-U facilitators? Can we recruit and retain sufficient primary care workers, community health workers and service users and their caregivers for outcome assessment?	PLWP can be adequately recruited, trained, and retained for delivering the SCAPE-U intervention For primary care workers, community health workers and service users and their families, maximum recruitment might be required to address loss to follow-up and drop-out	Process output: number of SCAPE-U facilitator recruited, completed training, and retained. Target = 50% retention For primary care workers, community health workers: number in health posts, number completing the training, supervision and completing outcome measures. Target for both = 60% at 8 months follow-up For SU and families: 50% completing the 5 session home visits	SCAPE-U facilitators, primary care workers, community health workers, service users and their families, research staffs
**3. Acceptability and feasibility measures and data collection procedures**	Are the quantitative and qualitative assessment measures and collection procedure acceptable and feasible to administer with the stakeholders at planned intervals?	The selected measures will be acceptable and feasible for measuring the intended outputs of the study	Tool completion rate, time, missingness of data (target: fewer than 20%)	Primary care workers, community health workers, service users and families, research staff
**4. Randomization**	Is cRCT feasible to run the study and measure the intended outcomes—in terms of contamination, fidelity, and implementation strategy?	Cluster randomization is feasible to execute the study and measure intended outcomes	Baseline summary of two arms Demographic details of primary care workers, community health workers (age, gender, years of experience, qualifications, education) Record on participant’s arm crossover (target: less than 30%)	Primary care workers, community health workers, service users and families, research staff
**5. Ethics and safety**	Can SCAPE-U be delivered with best ethical practice and safety of SCAPE-U facilitators, primary care workers, community health workers, service users and their families? Are there any unintended harms and how can they be addressed?	SCAPE-U intervention can be delivered with minimum harm to all stakeholders	Qualitative interviews Adverse event log Process notes	SCAPE-U facilitators, primary care workers, community health workers, service users and families, research staffs
**6. Change in outcome measures**	Do the outcome measures of the stakeholders improve after participating in the intervention?	Stakeholders in the SCAPE-U intervention arm will exhibit better outcomes than in control arm	Outcome measures assessment	Primary care workers, community health workers, service users and families
**7. Cost of intervention**	Can we measure the cost of SCAPE-U using measures and procedures from this study?	Costing of the intervention can be done in subsequent trial using procedures and measures tested in this pilot study	Cost-related outcome measures	YouBelong team, primary care workers, community health workers, service users and families

## Methods

### Setting

The study will be conducted within primary health facilities, community settings, and home settings in two urban and peri-urban districts of Kampala and Wakiso located in central Uganda, with district populations of 1,507,080 and 1,997,418, respectively [30]. Uganda’s formal health infrastructure consists of a tiered system of health centers based on the catchment area and services provided. At the lowest level, communities have village health teams consisting of volunteer community health workers tasked with coordinating health promotion activities and linking service users to care. Mental health services are meant to be provided at primary care centers (health centers III and IV) and hospitals (General, Regional and National Referral Hospitals). Services are provided by mental health professionals or general health workers depending on the tier. However, even though the integration of mental health services is part of national policy frameworks, mental health services are not well integrated into the primary health care system and are not routinely available at most health centers [31, 32]. Specialist mental health care is only accessible at two of the five national referral hospitals in the country and at 13 of 16 regional referral hospitals.

The study will be implemented by YouBelong Uganda, a Ugandan non-governmental organization involved in research, advocacy, and services for people with severe mental illness [33, 34], in coordination with the national health system and supported by the national referral psychiatric hospital at Butabika.

### Study design

The design is a cluster-randomized controlled feasibility trial comparing the standard implementation arm, where PCWs will be trained by mental health specialists, versus the intervention arm, where, in addition, PWLP will cofacilitate the PCWs training and provide home visits to the service users with psychosis.

The unit of randomization is a geographic cluster of primary care facilities. There are 36 primary care facilities in the two study districts. These will be divided into six geographic clusters based on a health subdistrict, each consisting of six primary care facilities. Three geographic clusters will be randomly allocated to the control arm and three to the SCAPE-U arm. We chose a cluster design because the interventions are delivered at a primary care facility and community level, meaning individual randomization is not possible. Having multiple health workers and primary care facilities in each cluster also ensures that we will not lose the entire cluster in the scenario that primary care workers or community health workers retire or are relocated by the government.

### Study participants

This study will involve six categories of study participants:(i)People with lived experience of psychosis trained as SCAPE-U facilitators—8 to 10 people with lived experience of psychosis who have previously received services from YouBelong Uganda [33, 35] will be recruited. The inclusion criteria are (1) diagnosis of a psychotic disorder confirmed by a mental health professional (psychiatric clinical officer or psychiatrist). (2) Capacity to provide informed consent. The main exclusion criterion is any health, functional, or cognitive impairment, assessed through mental state examination, that could jeopardize their full and safe participation in SCAPE-U activities. There are no inclusion/exclusion criteria relating to current engagement in treatment.(ii)Primary care workers—two primary care workers will be selected per health facility, with a target of 36 primary care workers per arm (72 total for the study). There are no exclusion criteria.(iii)Community health workers—we will select up to five community health workers from each health facility. This will equate to approximately 90 community health workers per arm and an estimated total of 180 community health workers for the study.(iv)Psychiatrists, psychiatric clinical officers,and psychiatric nurses—1 psychiatrist, 3 psychiatric clinical officers, and 2 psychiatric nurses who are involved in delivering training to primary care workers will be included.(v)Service users diagnosed with psychosis by primary care workers—the primary intended beneficiaries of study interventions are service users receiving treatment for psychosis at primary care facilities. The goal is to have 10 service users per cluster, 30 per arm, and 60 in total for the study. *Inclusion criteria*: (1) persons diagnosed with psychosis at a primary health care facility in Kampala/Wakiso District, following mhGAP training as part of the SCAPE-U trial; (2) ability of the service users to consent to study enrollment and procedures, or, if the service user does not have capacity to consent, a responsible surrogate can give consent; (3) persons eligible for outpatient management of psychosis. *Exclusion criteria*: (1) persons diagnosed with psychosis requiring inpatient management; and (2) persons for whom consent for participation in the study cannot be obtained.(vi)Family members of service users—at least one primary carer for study service users will be identified to collect outcome data from a family perspective (*n* = 30 per arm, 60 for the total study).

### Recruitment

Potential SCAPE-U facilitators will be identified and contacted by the YouBelong team. Potential service users’ participants will be identified by primary care workers working in participating health facilities. Their identification will commence after training of primary care and community health workers is complete. Following diagnosis of a service user with psychosis, as part of their usual practice, the primary care worker will contact the research assistant by telephone. The research assistant will either immediately attend the facility or arrange an alternative time to meet with the service user. Eligibility of service users will be assessed by research assistants, who will be psychiatric clinical officers by training. The research assistant will complete a screening assessment, including assessment of decision-making capacity using the University of California, San Diego Brief Assessment of Capacity to Consent (UBACC) [36]. Eligible potential participants will be given information about the study. Informed consent will be obtained for participants who are eligible and interested in participating. For all consenting participants, detailed contact information will be recorded.

### Sample size

We envision that the study sample size (60 service users and 60 linked family members) is sufficient to achieve our primary objectives, that is to assess SCAPE-U intervention acceptability and feasibility, as well as the trial and data collection procedures. This is a pilot cRCT and therefore we will not conduct a power calculation or formal hypothesis testing. Consistent with expert guidance on pilot trials, including the CONSORT extension for pilot and feasibility studies, this study is not powered to detect statistically significant between-arm differences [37]. Using an assumption of 80% participation rate, the sample size of 60 service users will enable the proportion of service users and carers who complete baseline assessments to be estimated with a 95% confidence interval width of 68.2% to 88.6%, using a Wilson score interval, which is appropriate given the small *n*. Estimates obtained in this feasibility trial will be used to inform the sample size determination for a fully powered RCT comparing the clinical and cost effectiveness of treatment as usual versus the SCAPE-U intervention.

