### Measures/outcomes for feasibility criteria and other objectives

The primary outcome of this trial is to understand the feasibility and acceptability of the SCAPE-U intervention. We have developed a set of quantitative and qualitative measures to do this as guided by recommendations from pilot study reporting [49]. These measures will determine what components of the SCAPE-U intervention will be included, excluded, or modified in the future full trial. The following quantitative criteria have been set to determine if this feasibility trial can be scaled up for a fully powered trial.Recruitment: at least 2 primary care workers were recruited in the study from each of the 36 health facilities selected.Retention: 50% of SCAPE-U facilitators retained by the end of PhotoVoice training, 60% of primary care workers, 60% of community health workers retained in post until the end of the 8 months follow-up period, and 50% of service users and families retained by the end of 5 session home visits.Contamination: less than 20% of cross-arm movement of primary care workers, community health workers, service users, and their families during the 8-month follow-up period.Cluster comparison: measuring baseline characteristics of recruited primary care and community health workers across both arms. We will collect information on primary care workers and community health workers’ education qualifications, gender, prior mental health training, age, and years of experience and determine balance between arms.Data collection procedure: less than 20% of missingness in collected data.Safety: fewer than 20% of adverse events among recruited SCAPE-U facilitators and service users.

Our qualitative criteria for this feasibility study are presented in Table 3.

**Table 3 Tab3:** Assessment of feasibility and acceptability of the intervention and trial procedures

Domains	Research questions	Methods
Feasibility and acceptability of SCAPE-U intervention	Do psychiatrist/psychiatric clinical officer, primary care workers, and mental health service users find it feasible and acceptable for PhotoVoice trained people with lived experience to participate as co-facilitators in training and supervision?	● Qualitative interviews with psychiatrist/psychiatric clinical officer, primary care workers, SCAPE-U facilitators, and research staff ● Process notes from trainings and supervision sessions

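### The sample-size interval prints a wrong upper limit (88.6% instead of 88.2%) and treats 60 service users in six clusters as independent

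*Protocol article*

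**What the plan says.** The Sample size section of the protocol article declines a power calculation, as is usual for a pilot, and rests the sample size on precision. It asserts that "the study sample size (60 service users and 60 linked family members) is sufficient to achieve our primary objectives". It then gives one calculation, for the share of users and their carers with a completed baseline. That share is expected "to be estimated with a 95% confidence interval width of 68.2% to 88.6%, using a Wilson score interval", on the stated assumption of 80% and n = 60. The section mentions no ICC, design effect or other allowance for clustering.

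The design is clustered. Under Study design, "Three geographic clusters will be randomly allocated to the control arm and three to the SCAPE-U arm". Under Study participants, "The goal is to have 10 service users per cluster, 30 per arm, and 60 in total for the study". The Data analysis section plans to estimate intra-cluster correlation coefficients for the later trial and fits health facility as a random effect in the PANSS analysis.

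**The concern.** Two things look wrong. First, method, level, proportion and n are all stated, so the interval is fully determined and can be checked; the printed upper limit does not follow from them. The sentence also presents a pair of limits as a width. Second, the calculation treats the users as 60 independent observations. They are found by the trained workers of facilities grouped into six randomized areas, and the protocol itself expects correlation within groups.

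What is at stake is the accuracy of a published precision claim, the only number offered in support of n = 60. If completion varies between clusters, the trial will estimate it less precisely than stated. No treatment comparison depends on this figure.

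**Working it through.** **Inputs.** From Sample size: p = 0.80, n = 60 (48 of 60), 95% level, Wilson score method, printed limits 68.2% and 88.6%. From Study design and Study participants: six clusters of m = 10 users. The ICC is not given; 0.01 to 0.10 is my assumption for illustration.

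**Step 1: the plan's own figure.** The Wilson limits are

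[p + z²/2n ± z·√(p(1−p)/n + z²/4n²)] / (1 + z²/n), with z = 1.96 and z² = 3.8416.

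- Denominator: 1 + 3.8416/60 = 1.0640
- Centre: (0.8 + 0.0320)/1.0640 = 0.7820
- Half-width: 1.96 × √(0.002667 + 0.000267)/1.0640 = 1.96 × 0.05416/1.0640 = 0.0998
- Limits: 68.2% and 88.2%; width 20.0 points

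The lower limit agrees with the protocol. The upper limit does not: 88.6 − 88.2 = 0.4 points.

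**Step 2: does another standard interval explain the pair?** For 48/60:

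| Method | Limits (%) |
|---|---|
| Wilson, continuity-corrected | 67.3 to 88.8 |
| Wald | 69.9 to 90.1 |
| Clopper-Pearson | 67.7 to 89.2 |
| Agresti-Coull | 68.1 to 88.3 |
| Jeffreys | 68.6 to 88.6 |
| Logit | 68.0 to 88.3 |

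None gives both printed limits.

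**Step 3: was clustering allowed for?** No. The printed lower limit equals the Wilson value for 60 independent users, and any design effect above 1 would lower it.

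**Step 4: allow for clustering.** Design effect = 1 + (m − 1) × ICC = 1 + 9 × ICC; effective n = 60/design effect, put into the Wilson formula. For ICC 0.05, the design effect is 1.45 and the effective n is 60/1.45 = 41.4. The centre is (0.8 + 0.0464)/1.0928 = 0.7745 and the half-width is 1.96 × 0.06654/1.0928 = 0.1193, giving 65.5% to 89.4%.

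| Assumed ICC | Design effect | Effective n | Limits (%) | Width (points) |
|---|---|---|---|---|
| 0 | 1.00 | 60.0 | 68.2 to 88.2 | 20.0 |
| 0.01 | 1.09 | 55.0 | 67.6 to 88.4 | 20.8 |
| 0.02 | 1.18 | 50.8 | 67.1 to 88.7 | 21.6 |
| 0.05 | 1.45 | 41.4 | 65.5 to 89.4 | 23.9 |
| 0.10 | 1.90 | 31.6 | 63.2 to 90.3 | 27.1 |

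The printed pair spans 88.6 − 68.2 = 20.4 points.

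**The case against.** The strongest reply is that little here matters. The slip is 0.4 points in one limit, and the printed span of 20.4 points is slightly wider than the correct 20.0, so the slip alone errs on the cautious side. That stands. The clustering effect rests on an ICC the protocol does not give and intends to estimate. At 0.01 or 0.02 the widths (20.8 and 21.6 points) are close to the printed one. That stands too. If correlation arose only within facilities, with 60/36 = 1.7 users each on average, even ICC 0.10 would give 67.8% to 88.4%. However, randomization and the recruitment target are set by the geographic cluster, so that is the level at which the precision should be stated.

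Several stronger readings are tempting and are not supported:

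- **That two interval methods were mixed.** The upper limit matches Jeffreys, but the lower one (68.6%) does not. A typing error explains the figure equally well.
- **That 60 is the wrong denominator.** The rate is called participation, and 60 is reached only after consent ("Informed consent will be obtained for participants who are eligible and interested in participating"). But the quantity named is baseline completion, for which enrolled users are a legitimate denominator. Using the 60/0.8 = 75 users who would have to be approached gives 69.6% to 87.5%, which is narrower, so this route does not show overstated precision.
- **That the calculation misses the one progression criterion for users**, "50% of service users and families retained by the end of 5 session home visits", which concerns the 30 users in the SCAPE-U arm. The same section also applies contamination, missing-data and safety thresholds that cover users. Missingness below 20% is the complement of 80% completeness.
- **That the true width is about 31 points.** That figure puts a t quantile on 5 degrees of freedom into the Wilson formula at ICC 0.05. The same substitution at ICC 0 already gives 25.9 points, so much of the excess comes from the quantile and not from clustering.

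**Conclusion.** The precision statement is wrong as written on two counts. The upper limit should be 88.2%, which is certain given the stated inputs but has no practical effect. The interval also assumes independence in a trial with six clusters of 10. Any positive ICC at cluster level widens it beyond 68.2% to 88.2%. The printed span is exceeded once the ICC passes roughly 0.005, since an effective n of 57 to 58 gives a width of 20.3 to 20.5 points.

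Over an assumed ICC of 0.01 to 0.10, the width is 20.8 to 27.1 points. This takes equal clusters of 10 and a Wilson formula with an effective sample size. The actual loss of precision is unknown until the ICC is estimated. A reader might infer that 60 users are too few. The documents do not support that: this is a feasibility trial without a power claim, and the defect lies in the precision reported for n = 60.

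**What to change.** In Sample size, change the upper limit to 88.2% and call the two figures limits. State that this interval assumes independent users. Then give the cluster-adjusted interval over an assumed ICC range, for example 67.6% to 88.4% at 0.01, 65.5% to 89.4% at 0.05 and 63.2% to 90.3% at 0.10, marking the ICC values as assumptions to be replaced by the trial's own estimate.

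This is a text change. The sample size of 60, the recruitment targets and the conduct of the trial are unaffected. The cost is a less favourable stated precision.
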